### Behavioural Outcomes

A number of behavioural outcome measures will be taken at baseline, 6 and 12 weeks, unless otherwise specified. The 24-item Bailey Dietary Screening Questionnaire will be used to identify nutritional risk. Three levels of nutritional risk include: at risk, possible risk, and not at risk. The measure has been found to have adequate sensitivity and specificity when compared with nutritional risk based on dietary reference intakes [47]. Sensitively measures indicate that 83% of individuals were correctly classified as positive by the screening tool. Specificity measures indicated 75% of individuals correctly classified as negative by the screening tool. An example item from the questionnaire is: “how often do you usually eat fruit as a snack?” Participants are asked to respond on a Likert scale ranging from 0 (never) to 4 (3 or more times a week).

An 18 item version of the *Three Factor Eating Questionnaire*, (TFEQ-R18), will be used to measure eating behaviour examining three cognitive and behavioural domains of eating; these include cognitive restraint, uncontrolled eating, and emotional eating. Good reliability has been reported [48]. An example of an item within the emotional eating scale includes “I start to eat when I feel anxious”. The item response occurs on a 4 point Likert scale from 1 (definitely true) to 4 (definitely false).

### Physical activity and diet intake diary

Prior to each clinic visit, participants will complete a 3 consecutive day record of their physical activity and dietary intake. Participants will complete the ‘food, drink and exercise diary’ record including 1 weekend and 2 week days [49]. For the physical activity section, participants will complete a 3-day activity log adapted from Bouchard and colleagues [50]. Participants will record an activity code from 1 to 9 that corresponds to the physical activity carried out during each five minute period; the time and activity of physical activity is thus recorded. In addition, participants will record their belief about the accuracy of their physical activity log. The physical activity log information will be assessed by examining energy expenditure. Each activity code is related to various levels of Metabolic Equivalent. The measure has been found to have high reliability with a coefficient of 0.96. For the food diary intake section, participants will record a 3-day food log containing information about their drink or food intake, time consumed, location, amount, drink or food description and method of preparation, and belief about the accuracy of their food log. The diary will be used to evaluate the participant’s compliance with the recommended diet and physical activity guidelines. The program Food Works will be used to analyse the food content and nutrients [49].

*Self-reported intervention compliance questions* were also incorporated at week 6 and 12. The 5 items will be used as a measure of the participant’s self-reported compliance to the behaviour changes of dietary intake and physical activity. For example, “on average, during the past 6 weeks, how often did you engage in at least 30 minutes of planned exercise?” with item responses ranging from 1 (7 days/week or Always) to 5 (Never).

### Psychological measures

Participants will be instructed to complete the outlined psychological measures before and after viewing the video presentation intervention unless specified otherwise. Variables from the HAPA will be measured to assess the psychological mediators that may explain the effects of the intervention on the behavioural and biomedical outcomes. The HAPA measures include items adapted from Barg and colleagues’ [51] measure of assessing risk perception for developing cancer for physically inactive middle aged adults. *Risk perception* will be assessed using four items on a 6 point Likert scale ranging from 1 (strongly disagree, much lower, not likely) to 6 (don’t know/refused) to measure perceived risk of developing obesity related risk factors. For example, “I think it is likely that I will develop health problems related to obesity at some point in my life.” *Outcome expectancy* will be assessed using six items with responses ranging from 1 (strongly disagree, not at all effective) to 5 (strongly agree, extremely effective) to question participants about the effect of diet and physical activity on health risks related to weight gain. For example, “I think that consuming fewer calories per day is a very important way to help me to lose weight”. *Intention* will be assessed with four items that ask participants how much they plan and intend to follow the diet guidelines and/or to participate in the recommended physical activity amount over the next 12 weeks. Responses range from 1 (strongly disagree) to 5 (strongly agree). For example, “I intend to participate in daily physical activity with a minimum of 30 minutes of planned exercise on each individual occasion over the next 6 weeks. *Action self-efficacy* will be measured using 10 items regarding participants’ confidence and ability to engage in the recommended diet and physical activity guidelines over the next 12 weeks. Prior to answering the questions, participants would have heard the recommendations during the video presentation. Items are on a 5 point Likert scale ranging from 1 (not confident, not likely, strongly disagree) to 5 (completely confident, extremely confident, strongly agree). For example, “if it were entirely up to you, how confident are you that you would be able to follow a diet that requires you to consume fewer calories per day on each individual occasion over the next 6 weeks?” *Maintenance self-efficacy* will be measured using 18 items on a 5 point Likert scale ranging from 1 (not confident) to 5 (completely confident) to measure barriers to engage in the recommended physical activity or diet guidelines. For example, participants were asked “How confident are you that you will do daily physical activity with a minimum of 30 minutes of planned exercise during your leisure time on each individual occasion over the next 6 weeks even if…” followed by a list of barriers, such as, but not limited to bad weather and feeling tired. The participants *planning* will be assessed using two items ranging from 1 (strongly disagree) to 5 (strongly agree) that ask participants if they had made a detailed plan about when, where and how they would engage in physical activity or follow the diet guidelines. For example, “I have made a detailed plan about when, where, and how I will do daily physical activity with a minimum of 30 minutes of planned exercise on each individual occasion over the next 6 weeks”.

Further variables that relate to the HAPA were adopted from Hagger and colleagues [32]. *Motivation* will be assessed at baseline by asking participants to respond to six items that question motivation to participate in physical activity and change their diet. For example, “how motivated are you to change your diet on each individual occasion over the next 12 weeks?” Item responses are based on a 6 point Likert scale ranging from 1 (not at all motivated, no effort at all) to 6 (extremely motivated, all my effort). In addition four items exploring engagement in mental imagery exercises will be used. Participants will be asked to indicate the level to which they were able to imagine the task. For example, “to what extent did you visualise in your mind (imagine) exactly how you might reach your diet goals (example, consuming fewer calories per day) on each individual occasion over the next 6 weeks?” The items are on a 6 point Likert scale ranging from 1 (indicating did not imagine), to 6 (indicating clearly imagined).

*Goal setting* will be measured by asking participants six open ended questions. For example, ‘What are your goals for physical activity?’ The answers to these questions will be “coded” appropriately based on whether they are appropriate and realistic. *Intervention checks* will also be included to ensure that participants engaged with and completed the implementation intention and mental imagery exercises appropriately and according to protocol. That is, participants will be asked to record their goals; If-then plans; and a list of the steps they imagined during the intervention process. The answers to these questions will be “coded” appropriately based on whether they are appropriate and realistic. These variables will be measured as they are expected to mediate the key components of the intervention. That is, the effect of the mental imagery component of the intervention variable on the primary and secondary outcomes is expected to mediate the HAPA variables of self-efficacy, motivation, outcome evaluation, and intention. Similarly, the effect of the if-then plan component of the intervention on the primary and secondary outcomes is expected to be mediated by the HAPA planning variable.

Imagery ability will be measured at baseline as it may moderate the effectiveness of the mental imagery intervention and should therefore be included as a potential covariate. Imagery ability will be measured using the *Betts Questionnaire upon Mental Imagery* [52] is a 35 item questionnaire used to measure the clarity and vividness of their mental imagery ability. The questionnaire instructs participants to imagine, for example “Visualize a mental image of a friend you see on a regular basis” and rate the image vividness on a Likert scale. Sheehan suggests that the measure is valid and has predictive value. The scale has also been found to be reliable [53].

The variables of quality of life, depression, anxiety, and stress will be measured as a control variables to ensure the intervention does not have adverse effects on quality of life or emotion. These variables will be measured using the two listed questionnaires. *The Impact of Weight on Quality of Life Questionnaire (IWQOL - Lite)* is a 31 item version, self-reported measure that assesses the effect of obesity on quality of life in five domains: physical function, self-esteem, sexual life, public distress, and work [54]. For example, a physical function item includes “because of my weight I have difficulty picking up objects” with responses made on 5 point Likert scales ranging from 1 (never true) to 5 (always true). *Depression Anxiety Stress Scales-21* (DASS-21) will be used to measure symptoms of depression, anxiety, and stress. At baseline, 6 and 12 weeks, participants will rate their symptoms over the past week by answering 21 items using a 4-point Likert Scale anchored by 0 (did not apply to me at all) and 3 (applied to me very much, or most of the time) [55]. An example item from the questionnaire includes “I couldn’t seem to experience any positive feeling at all”.

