## Intervention

### Weight-loss information for all participants

Participants will be presented with a psycho-educational component common to all intervention conditions followed by, if assigned to the intervention conditions, the behaviour change components based on the HAPA. The components will be delivered by an interactive video presentation by an investigator. Table 1 outlines the components specific to each of the three study conditions.

The significance of adopting theory-based intervention techniques delivered by video means that the intervention is evidence-based, cost effective, requires minimal contact with the participant, provides flexibility for delivery, and is easily available. The video presentation allows messages to be conveyed in a consistent manner and reduces experimenter bias and provides greater control over potential variation in delivery across participants. All participants will receive identical content in relation to study design, psycho-education information, dietary intake and physical activity guidelines. Thus differences between the control and intervention conditions can be attributed purely to the intervention components. The participants in the two intervention conditions will receive the same information regarding the mental imagery and implementation intentions instructions, and thus differences in these intervention conditions can be attributed to the goal reminder text messages and not differences in intervention delivery style.

The main components of the video presentation are outlined below^a^. The pre-recorded video presentation provided to participants within all conditions, will introduce participants to study information and basic concepts of weight loss including psycho-education. The participants will be informed that they will be required to adhere to two guidelines for physical activity and dietary intake, respectively, in accordance with the weight-loss intervention.

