#### Statistical analysis

A series of 3 (condition: control, intervention, and intervention with text message) × 2 (time: 6 and 12 weeks) mixed model multivariate analyses of covariance (MANCOVAs) with time as a repeated measures variable will be used examine the effects of the intention over time on study outcome variables. Baseline measures will be covariates in the model. A separate MANCOVA will be conducted for each set of dependent outcome variables: biomedical, behavioural and psychological. Pending significant multivariate effects, follow-up univariate analysis of covariance (ANCOVAs) will be used to identify differences for individual variables within each outcome set. Post-hoc follow-up tests will also be conducted to locate individual differences at the time intervals. Mediation analyses will be conducted by mediated multiple linear regression analysis with dummy-coded intervention conditions as the independent predictor variables, the constructs from the HAPA included as mediating variables, and the primary and secondary biomedical outcome variables as the dependent variables. Mediation will be confirmed through significant bootstrapped indirect effects using Preacher and Hayes’ [56] algorithms for multiple mediation and the PROCESS macro. Missing data will be handled by multiple imputation using regression analysis with the Markov-chain Monte Carlo (MCMC) estimation method. In addition, we will adopt a full intention-to-treat analysis with last measured data points carried forward in order to provide a conservative estimate of the effects.

Sample size has been determined by a power analysis using the G*Power 3.1 Program, suitable to evaluate differences between the three condition levels greater than 10%, with statistical power set at > 0.80 and alpha set at *p* < .05 [57]. A large effect size is assumed as previous studies that have used implementation intentions and reminder text messages [31], as well as studies using mental imagery and implementation intentions to increase exercise behaviour [58], have found large effect sizes. Given the estimated effect size, the total sample size required post-test is 66 and considering a potential 35% drop out rate and eliminations of cases due to missing data or spoilt questionnaires based on previous trials [21], we plan to recruit 102 participants at baseline or until the required sample size has been achieved.

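### The mediation plan credits separate paths to if-then planning and to imagery, which the three arms cannot separate, and the mediation regression is listed without baseline covariates

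*Protocol article*

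**What the plan says.** Under Psychological measures, the protocol article links each technique to its own mediators. For if-then plans it says "the effect of the if-then plan component of the intervention on the primary and secondary outcomes is expected to be mediated by" and then names only the planning construct. For imagery it says "the effect of the mental imagery component of the intervention variable on the primary and secondary outcomes is expected to mediate the HAPA variables"; the four constructs it goes on to list are intention, outcome evaluation, motivation and self-efficacy. As printed, that second sentence runs in the reverse direction, but the if-then sentence that follows it shows what is meant. The Hypotheses section repeats the pairing for planning, self-efficacy and motivation.

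On the arms, Table 1 lists implementation intentions and mental imagery together in both intervention conditions and in neither form for control. The section on weight-loss information for all participants confirms it: "The participants in the two intervention conditions will receive the same information regarding the mental imagery and implementation intentions instructions".

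Under Statistical analysis, mediation is to be tested by "mediated multiple linear regression analysis with dummy-coded intervention conditions as the independent predictor variables". The remaining terms of the model are listed as "the constructs from the HAPA included as mediating variables, and the primary and secondary biomedical outcome variables as the dependent variables". The decision rule is: "Mediation will be confirmed through significant bootstrapped indirect effects". The sentence "Baseline measures will be covariates in the model" belongs to the MANCOVA and is not repeated for the mediation model.

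The HAPA measures are taken before and after the video unless otherwise stated. Motivation is described as assessed at baseline.

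**The concern.** There are two linked problems.

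First, a statement that one component works through one mediator needs a contrast in which that component varies while the other does not. This trial has no such contrast. A significant indirect effect through planning would be an effect of imagery and if-then plans delivered together, and the stated expectations invite readers to credit it to if-then plans alone.

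Second, randomisation protects the path from condition to mediator but not the path from mediator to outcome, because people are not randomised to their level of self-efficacy or planning. Eligible BMI runs from 25 to 40, so starting weight varies widely. If starting weight or starting mediator level is related to both the later mediator and the later outcome, leaving them out can produce an apparent indirect effect. If they are unrelated to the mediator, leaving out baseline weight still costs precision.

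At stake is the mechanism claim, which the article presents as a distinctive contribution of the trial.

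**Working it through.** **1. Can the components be separated?** Code each arm from Table 1:

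| Arm | Intercept | Imagery | If-then | Text |
|---|---|---|---|---|
| Control | 1 | 0 | 0 | 0 |
| Intervention | 1 | 1 | 1 | 0 |
| Intervention with text | 1 | 1 | 1 | 1 |

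The imagery and if-then columns are identical, so the matrix has rank 3 with 4 columns. Two contrasts are estimable: package against control, and text against no text within the package.

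The mediators cannot stand in for the components. In Table 2 the imagery task rehearses the steps of the participant's own if-then plan, and the Background describes process imagery as mainly a planning strategy. Imagery could therefore raise planning scores. The text messages do not help, since their content covers both techniques.

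**2. The plan's own sample size.** The article gives 66 at post-test and 102 recruited. Taking a large effect as Cohen f = 0.40 (assumed; the article gives no number), a one-way three-group F test at alpha 0.05 has power 0.818 at N = 66, and 66 / 0.65 = 101.5, rounded up to 102. Both figures reproduce, and this point does not change them.

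**3. What the listed mediation model does without baseline terms.** As listed, with D1 and D2 the arm dummies:

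- Mediator: M = a0 + a1·D1 + a2·D2 + error
- Outcome: Y = c0 + c1·D1 + c2·D2 + b·M + error
- Indirect effects: a1·b and a2·b

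The adjusted version adds baseline weight and baseline mediator to both equations.

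Precision: if baseline and follow-up weight correlate at r, omitting baseline weight inflates the residual variance by about 1/(1 - r²). That is 2.8 at r = 0.80, 5.3 at 0.90 and 10.3 at 0.95.

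Simulation: 66 participants in three equal arms, 4,000 replicates per scenario and one mediator. Assumed inputs in SD units were a mediator baseline-to-follow-up correlation of 0.6, an arm effect on the mediator of 0.8, and weight r of 0.80 to 0.95. Significance meant both paths exceeding |t| = 2.0, as a stand-in for the bootstrap.

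Share of trials declaring mediation when none exists (unadjusted / adjusted):

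| Weight r | Baseline mediator-weight correlation 0 | -0.2 | -0.4 |
|---|---|---|---|
| 0.80 | 3.5% / 4.4% | 8.2% / 4.6% | 24.2% / 4.1% |
| 0.90 | 3.6% / 4.6% | 10.0% / 4.6% | 30.6% / 4.2% |
| 0.95 | 3.8% / 4.5% | 10.0% / 4.6% | 33.0% / 4.8% |

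In the two right-hand columns the unadjusted mean indirect effect is -0.075 to -0.183, where the truth is 0. The adjusted mean stays within 0.001 of 0.

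Power for a true indirect effect of -0.12 with the baseline mediator-weight correlation at 0:

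| Weight r | Unadjusted | Adjusted |
|---|---|---|
| 0.80 | 16.2% | 29.2% |
| 0.90 | 16.1% | 49.6% |
| 0.95 | 15.6% | 73.4% |

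Where that correlation is not 0, the unadjusted model sometimes rejects more often than the adjusted one, but its mean estimate is then -0.195 to -0.302 against a true -0.12.

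**The case against.** The strongest reply on components is that the article states a theoretical expectation, while the planned regression uses condition dummies, which do estimate package effects. It also describes the two techniques as acting in synergy. That is fair, and no sentence says that a planning path will be reported as proof of the if-then component. But the expectation is attached to named components and mediators, and the mediation analysis is the only one offered to test it. The mismatch between claim and design stands.

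On baseline terms, the reply is that two sentences in an article are not a full model specification, and the abstract speaks of controlling for baseline values when comparing conditions. This also has force. A reader might infer that the mediation model is deliberately unadjusted; the article does not say so, and a fuller plan could add the terms. What stands is that the model as listed lacks covariates that the same section states for the MANCOVA.

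Other stronger readings are tempting but not supported:

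- That follow-up weight is regressed on cognitions measured at the same visit. The article fixes neither the mediator's time point nor whether the outcome is a level or a change, and post-video scores exist.
- That a planned moderation question goes unanswered. Imagery ability is measured "as it may moderate the effectiveness of the mental imagery intervention and should therefore be included as a potential covariate". That reasoning is loose, since a covariate does not test moderation, but the Hypotheses section contains no moderation hypothesis.
- That the number of possible indirect effects is part of this fault. Multiplicity is a separate matter.

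**Conclusion.** The point holds in two parts of unequal certainty.

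The component part is firm and rests only on Table 1 and the stated pairings: component-specific mediation is not identifiable from these arms.

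The baseline part is a worthwhile correction to the model as listed. Its direction follows from the mediator not being randomised, but its size is not known. The simulated rates rest on assumed correlations, a single mediator and a substitute for the bootstrap. If baseline mediator and baseline weight are uncorrelated, the harm is lost power and not false mediation.

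As written, motivation cannot mediate a later effect if it is assessed only at baseline.

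Mediation is a secondary analysis. A reader might infer that the body-weight comparison or the sample size is compromised; neither is affected.

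**What to change.** - State every indirect effect as an effect of the combined package against control, or of adding text messages to the package. Remove component-specific mediation claims from the Hypotheses and Psychological measures sections, and correct the direction of the imagery sentence.
- Add the baseline value of the outcome and the pre-video score of the mediator, where one is collected, as covariates in both mediation equations. Confirm whether action self-efficacy has a usable pre-video score, because the article says its items are answered after participants have heard the recommendations in the video.
- Treat motivation as a mediator only if it is also measured after the intervention; otherwise remove it from the mediator list.

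The first two changes are to wording and model specification, and use data the article already plans to collect. Measuring motivation after the intervention, if not already intended, would add six items to a later questionnaire. The price is narrower claims about single techniques.

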**Methods/Design:**

Overweight or obese participants will be randomly allocated to one of three conditions: (1) a psycho-education plus an implementation intentions and mental imagery condition; (2) a psycho-education plus an implementation intentions and mental imagery condition with text messages; or (3) a psycho-education control condition. The intervention will be delivered via video presentation to increase the intervention’s applicability in multiple contexts and keep costs low. We hypothesise that the intervention conditions will lead to statistically-significant changes in the primary and secondary outcome variables measured at 6 and 12 weeks post-intervention relative to the psycho-education control condition after controlling for baseline values. The primary outcome variable will be body weight and secondary outcome variables will be biomedical (body mass, body fat percentage, muscle mass, waist-hip circumference ratio, systolic and diastolic blood pressure, low-density lipoprotein, high-density lipoprotein, total cholesterol, triglycerides, blood glucose and insulin levels), psychological (quality of life, motivation, risk perception, outcome expectancy, intention, action self-efficacy, maintenance self-efficacy, goal setting and planning), and behavioural (self-reported diet intake, and physical activity involvement) measures. We also expect the intervention condition augmented with text messages to lead to statistically significant differences in the primary and secondary outcome variables at the follow up periods after controlling for baseline values.

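### Quality of life and DASS-21 are collected to check for harm, but the plan looks at single psychological variables only after a significant multivariate test

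*Protocol article*

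**What the plan says.** Under Psychological measures, the protocol article gives the quality-of-life and mood scales a purpose: they "will be measured as a control variables to ensure the intervention does not have adverse effects on quality of life or emotion". The instruments are IWQOL-Lite for quality of life and DASS-21 for depression, anxiety and stress. For DASS-21 the schedule is explicit: "At baseline, 6 and 12 weeks, participants will rate their symptoms over the past week by answering 21 items".

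The abstract (Methods/Design) lists the psychological secondary outcomes as "psychological (quality of life, motivation, risk perception, outcome expectancy, intention, action self-efficacy, maintenance self-efficacy, goal setting and planning". That is nine variables: quality of life is among them, and depression, anxiety and stress are not.

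The Statistical analysis section then fixes the route to a result:

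- The joint tests are defined by outcome set: "A separate MANCOVA will be conducted for each set of dependent outcome variables: biomedical, behavioural and psychological".
- On adjustment, the wording is: "Baseline measures will be covariates in the model".
- The step from a set to its single variables is conditional: "Pending significant multivariate effects, follow-up univariate analysis of covariance (ANCOVAs) will be used to identify differences for individual variables within each outcome set".

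The post-hoc tests mentioned there locate differences between time points within the same chain. The mediation models use HAPA constructs as mediators and biomedical variables as outcomes. Neither gives IWQOL-Lite or DASS-21 a route of its own.

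**The concern.** A multivariate test ahead of single-variable tests is there to limit false claims of benefit. A harm check has the opposite priority, since the costly error is to miss a signal. As the plan is written, a worsening in quality of life is examined on its own only if nine variables, most of them motivation, belief and planning scales, differ jointly between arms. Whether harm is looked for then depends on whether those other scales respond.

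DASS-21 is in a similar or worse position. It sits under the Psychological measures heading, so it can be read into the psychological set; it then meets the same condition and adds dimensions to the joint test. If the abstract's list is taken as the set, DASS-21 has no stated comparison.

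At stake is the purpose the protocol itself gives these scales. Table 1 limits what that purpose can cover. Psycho-education, weight-loss guidelines and goal setting go to all three arms, so a comparison between arms bears on if-then planning, mental imagery and text messages, and not on calorie restriction.

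**Working it through.** **The plan's own figures.** The Statistical analysis section gives 66 participants post-test, 35% loss and 102 recruited, "with statistical power set at > 0.80 and alpha set at *p* < .05". It assumes a large effect without a number; I take Cohen's f = 0.40. For a one-way comparison of three groups, the noncentrality is f² × N = 0.16 × 66 = 10.56 on 2 and 63 degrees of freedom, which gives power 0.818. The smallest balanced N with power of at least 0.80 is 66. Then 66 / (1 − 0.35) = 101.5, rounded up to 102. Both figures reproduce and are not in dispute. Equal arms (an assumption, as no ratio is stated) give 66 / 3 = 22 per arm.

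**Direct test of one scale.** For a two-sample t test of one active arm against control, noncentrality = d × √(22/2).

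- d = 0.8: 0.8 × 3.317 = 2.65, power about 74%.
- d = 0.5: 0.5 × 3.317 = 1.66, power about 37%.

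**The same test behind the multivariate condition.** This is a simulation with 22 per arm and a three-group Wilks test at 0.05. There are 9 outcomes (the named set) or 12 (with the three DASS-21 scales added), and inter-scale correlation is 0.3. One arm is worse on one scale. A harm counts as detected if both the Wilks test and that scale's own test are significant. The two right-hand columns give the percentage of trials in which the harm is detected.

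| Other psychological scales | Harm | Direct | Behind the condition |
|---|---|---|---|
| None responds | 0.8 SD | about 74% | about 32-38% |
| None responds | 0.5 SD | 36-37% | 9-10% |
| Three improve by 0.5 SD in both active arms | 0.8 SD | 73-75% | about 60-65% |
| Three improve by 0.8 SD in both active arms | 0.8 SD | about 74% | 72-73% |

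**Sensitivity.** With harm in both active arms, baseline-adjusted models, correlation from 0 to 0.5 and no other scale responding, a 0.8 SD harm is detected directly in 75-77% of trials. Behind the condition the figure is 25-45% with 9 outcomes and 20-34% with 12. For the row with a 0.5 SD benefit, allowing correlation 0 as well as 0.3 and either direction of harm widens 60-65% to 50-65%.

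**What a non-significant result could exclude.** The 95% interval half-width for an arm difference is 1.99 × √(2/22 × (1 − r²)), where r is the correlation between baseline and follow-up.

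- r = 0: 1.99 × 0.3015 = 0.60 SD.
- r = 0.7 (assumed): 0.60 × √0.51 = 0.43 SD.

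An observed difference of zero would therefore still be compatible with a harm of roughly 0.4 to 0.6 SD.

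**The case against.** The strongest objection is that the large loss needs a setting the trial does not expect. The Hypotheses section predicts effects on planning, self-efficacy and motivation, all in the same set, and the sample size rests on a large effect. If those scales respond strongly, the multivariate test is nearly always significant and the condition costs almost nothing. This stands, and the table shows it. It does not remove the point: the check is weakest when the programme does not move its target constructs, and a harm check should not depend on that.

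A second objection is that a journal article may leave the harm analysis to a fuller plan. For DASS-21 read as outside the set, that has force, since silence alone is not an error. For quality of life, however, the article states the condition, so a fuller plan would have to make an exception to it.

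A third is that the interval width reflects sample size and remains after any change. That is correct. It is a reason to report limits, not evidence against the multivariate condition.

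Three stronger readings are tempting and are not supported:

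- A reader might infer that the trial would declare the programme harmless after a non-significant test. No section says so; the stated aim explains why the scales are collected and is not a decision rule. Nor does anything bar descriptive reporting by arm.
- A reader might take the label of control variables to mean adjustment for follow-up values. The Statistical analysis section names only baseline measures as covariates.
- A reader might fear missed harm from calorie restriction. All arms receive that guidance, so neither the planned comparison nor the one proposed below could show it.

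**Conclusion.** The point holds in limited form. The protocol article gives IWQOL-Lite and DASS-21 a harm-check purpose, and its analysis rule makes the individual test of quality of life conditional on an omnibus efficacy result. DASS-21 is either under the same rule or without a stated comparison.

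For a 0.8 SD harm on one scale in one arm, the condition roughly halves detection if nothing else in the set responds. It removes about a tenth to a fifth of it if three other scales improve by 0.5 SD, and almost none if they improve by 0.8 SD. These figures assume complete data on 66 participants, equal arms, inter-scale correlation 0.3, harm confined to one scale, and the condition effect tested without modelling the two time points separately. The structural point does not depend on them.

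The plan should be changed here, but this is not a fatal flaw. It concerns the added components only, and the data needed are already to be collected.

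**What to change.** State the role of IWQOL-Lite and DASS-21 in the analysis, and exempt them from the requirement of a significant multivariate test. For each scale, report the baseline-adjusted difference of each active arm from control at weeks 6 and 12 with a 95% confidence interval, whatever the MANCOVA shows. Base any statement about absence of harm on the interval limits, not on non-significance, and say that it refers to the planning, imagery and text-message components.

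The cost is one extra table from data already planned. Without multivariate protection there will be somewhat more chance signals on these scales, which is acceptable for a harm check if the table is labelled as such.
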